#### Criteria for discontinuing or modifying allocated interventions {11b}

##### Drop out criteria

Subjects can leave the study at any time for any reason if they wish to do so without any consequences. The parents/guardians of children under the age of 16 can also decide to withdraw their child from the study at any time for any reason without any consequences. The investigator can decide to withdraw a subject from the study for urgent medical reasons.

#### Strategies to improve adherence to interventions {11c}

Not applicable.

#### Relevant concomitant care permitted or prohibited during the trial {11d}

All concomitant care is permitted.

#### Provisions for post-trial care {30}

There will be no separate insurance for subjects participating in this study. The risks associated are not increased, because regular treatment is used in both groups and the VR goggles are just used to distract patients. A request for dispensation from the statutory obligation to provide insurance has been approved. Cover for damage to research subjects through injury or death caused by this study is provided by the liability insurance of the Amphia Hospital.

### Outcomes {12}

The main study outcome parameter is the difference in post-procedural anxiety scores in the intervention and control groups, using the Child Fear Scale (CFS) [15]. The secondary study parameters are the differences between the two groups in anxiety reduction (difference between the child’s CFS score pre- and post-procedural), NRS pain given by the child (pre- and post-procedure), NRS Satisfaction Score given by the child and accompanying parent/guardian and the child’s fastest heart rate measured by a finger pulse oximeter during the procedure.

The following demographic data is collected from the patient’s medical records: date of fracture, date of plaster intervention, age, sex, upper or lower extremity fracture, specific location of the fracture, type of plaster treatment (plaster replacement or removal) and previous experiences with plaster removal. After randomisation, additional demographic data is collected from the patient or accompanying parent/guardian and the orthopaedic practitioner before the plaster intervention (e.g. the use of pain killers, method of plaster removal, and the video chosen (if assigned to the intervention group)).

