### Objectives {7}

The primary objective of this study is to evaluate the difference in the post-procedural anxiety level in children in the plaster room with or without distraction with use of VR. The secondary objectives of this study include anxiety reduction (difference between CFS scores pre- and post-procedural), level of pain experienced (using the numeric rating scale (NRS)), satisfaction scores (NRS) given by the child and the accompanying parent/guardian and the child’s fastest heart rate measured by a finger pulse oximeter during the procedure.

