#### Intervention description {11a}

The investigational group will receive standard care and will wear the VR goggles and headphones as well as a finger pulse oximeter during the plaster procedure. The VR goggles will play a video during the procedure to distract the child. The headphones will make sure that the child is more focused on the video by playing the sound of the video and by drowning out the noise of the procedure.

The control group will receive standard care and will wear the finger pulse oximeter.

Each age group (5–11 and 12–17) will have a choice between two videos of approximately 20 min long. The video length is based on the maximum length of the plaster intervention. The children can choose between single episodes of different series on Netflix. The content of the video is based on Netflix recommendations and is screened to make sure the content is appropriate for the hospital setting and the age group.

Children between the ages of 5 and 11 years have a choice between Masha and the Bear season 1 episode 2 and The Thundermans season 1 episode 2; children aged 12–17 years can choose between Modern Family season 1 episode 2 and Brooklyn Nine-Nine season 1 episode 2.

Masha and the Bear is an animated series that focusses on the adventures of a little girl named Masha and a fatherly bear that keeps her safe and prevents disasters. The Thundermans is a comedy series that revolves around the Thundermans, a family with superpowers who try to live normal lives. The spoken language of both videos is set to Dutch.

Modern Family is a sitcom and follows the lives of three diverse families and is filmed from the perspective of an unseen documentary maker. Brooklyn Nine-Nine is a comedy series following the immature but talented NYPD detective Jake Peralta and his diverse, lovable colleagues as they police the NYPD’s 99th precinct. The spoken language of both videos is set to English with Dutch subtitles.

Before the procedure, the child’s anxiety and pain scores are collected with a short questionnaire, using the Child Fear Scale (CFS) [14] and the Numeric Rating Scale (NRS pain), respectively. Then, the orthopaedic practitioner explains the plaster procedure, the finger pulse oximeter is put on and the randomisation result is revealed.

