### Sample size {14}

The expected anxiety score (CFS) in the control group is on average 1.78 ± 1.40 [11]. For an intended improvement by 0.5 (i.e. to 1.28) on the Child Fear Scale, with a statistical power of 80% and an alpha of 0.05, a sample size of 123 participants is needed in each group. To anticipate a 10% dropout, we will include 135 children in each group.

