#### Concealment mechanism {16b}

The randomisation is done in Castor EDC. Each patient is randomised after the investigator receives the completed written informed consent forms from the child and/or parent/guardian present and after the first questionnaire is completed. Therefore, the randomisation allocation is not revealed until the patient is included in the study to ensure the allocation group has no effect on the participant’s decision.

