## Statistical methods

### Statistical methods for primary and secondary outcomes {20a}

The outcomes of both groups will be compared with the use of an independent samples *t*-test or a Mann-Whitney *U* test, depending on the distribution of the data, assessed using a histogram and an independent samples Kolmogorov-Smirnov (K-S test). If the data is normally distributed, an independent *t*-test will be performed, and the mean and standard deviation will be reported. If the data is not normally distributed, a Mann-Whitney *U* test will be performed, and the median and (interquartile) range will be reported.

The statistical package SPSS (version 25, IBM Corp, Armonk, NY, USA) will be used for all statistical analyses. *P*-values < 0.05 are considered significant for the primary outcome. The significance level of the secondary outcomes will be adjusted to multiple testing according to the Holm method [14].

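### The primary comparison leaves out the pre-randomisation fear score and the age stratum: a valid test, but one that gives up precision at no saving

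*Protocol article*

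**What the plan says.** All references are to the protocol article.

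- **Primary outcome** (Outcomes {12}): "The main study outcome parameter is the difference in post-procedural anxiety scores in the intervention and control groups", on the CFS.
- **Test** (Statistical methods {20a}): "The outcomes of both groups will be compared with the use of an independent samples" t-test, or a Mann-Whitney U test if the data are not normal. Neither takes a covariate. The section on additional analyses {20b} adds descriptive statistics and subgroups, but no adjusted analysis.
- **Baseline measurement** (Intervention description {11a}): "Before the procedure, the child’s anxiety and pain scores are collected with a short questionnaire, using the Child Fear Scale (CFS" and a pain scale.
- **Timing** (Concealment mechanism {16b}): a child is randomised once consent forms are in "and after the first questionnaire is completed". The first CFS is therefore a true pre-randomisation covariate.
- **Only stated outcome use of the baseline CFS** (Outcomes {12}): the secondary outcome "anxiety reduction (difference between the child’s CFS score pre- and post-procedural".
- **Stratification** (Trial design {8}, Sequence generation {16a}): by age group, 5–11 and 12–17, because age may affect the outcomes. Baseline fear is not a stratification factor.
- **Sample size** (Sample size {14}): "The expected anxiety score (CFS) in the control group is on average 1.78 ± 1.40", an intended improvement of 0.5, 80% power, alpha 0.05, 123 per group, raised to 135.

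**The concern.** The trial collects a covariate on the same scale as the primary outcome, at the same visit and before allocation, and then leaves it out of the comparison that decides the trial. The age stratum, used to balance the arms, is left out too. If pre- and post-procedure fear are correlated, part of the outcome variation is predictable from data already in hand. Leaving it in the error term widens the confidence interval. It also means that a chance difference in starting fear between the arms passes partly into the estimated effect, and stratifying by age does not directly guard against that. The trial is sized at 80% power with little reserve, so extra precision at no cost is worth having.

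Because the protocol names the test, this is a stated choice and not a detail left to an analysis plan.

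**Working it through.** **Inputs.** From Sample size {14}: difference δ = 0.5, SD σ = 1.40, alpha 0.05, 123 per group, 135 after the dropout allowance. Sidedness is not stated. Two-sided is assumed, since it reproduces the planned size (one-sided gives 97). The pre-post correlation r is not in the document, so a range is shown. Equal SD before and after is also assumed.

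**Step 1: the plan's own figure.** n per group = 2 × [1.40 × (1.960 + 0.842) / 0.5]² = 123.07. The stated 123 reproduces, with power 79.98% by the normal approximation. It corresponds to an unadjusted comparison with the full SD.

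**Step 2: evaluable number.** 135 less 10% is 121.5, taken as 121 per arm.

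**Step 3: power at 121 per arm.** The standard error is s × √(2/121), and power comes from the t distribution with that standard error. The SD s is:
- post score, unadjusted: s = σ = 1.40, so SE = 0.180 and δ/SE = 2.78;
- ANCOVA on baseline CFS: s = σ√(1 − r²);
- change score: s = σ√(2 − 2r).

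| assumed r | unadjusted post score | ANCOVA: s | ANCOVA: power | change score: s | change score: power |
|---|---|---|---|---|---|
| 0.1 | 79% | 1.393 | 79.4% | 1.878 | 54% |
| 0.2 | 79% | 1.372 | 80.6% | 1.771 | 59% |
| 0.3 | 79% | 1.336 | 83% | 1.657 | 65% |
| 0.5 | 79% | 1.212 | 89% | 1.400 | 79% |
| 0.7 | 79% | 1.000 | 97% | 1.084 | 95% |

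The variance of the estimate falls by r²: 9%, 25% and 49% at r = 0.3, 0.5 and 0.7. That is worth 1/(1 − r²) − 1 = 10%, 33% and 96% more children.

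**Step 4: why the change score is no substitute.** ANCOVA variance is proportional to 1 − r² = (1 − r)(1 + r), and change-score variance to 2(1 − r). Since 1 + r is below 2 for any r below 1, ANCOVA is the more precise. Below r = 0.5 the change score is also less precise than the plain post score.

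**Step 5: chance imbalance.** If the baseline SD is also 1.40, the difference in mean baseline CFS between arms has SE 0.180, so 95% of chance imbalances lie within ±1.96 × 0.180 = ±0.35 points. An imbalance at that limit shifts the unadjusted difference by r × 0.35, or about 0.11, 0.18 and 0.25 points at r = 0.3, 0.5 and 0.7. Against the target of 0.5 that is 21%, 35% and 49%.

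The effect of adding the age stratum cannot be quantified, because the document gives no figure for the relation between age and CFS.

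**The case against.** The strongest reply is that nothing is wrong with the planned test. It is unbiased over randomisation and holds its type I error, and its standard error already covers chance imbalance. The trial was sized for exactly this comparison and essentially meets its 80%. All of that stands. A reader might infer from the omission that the primary analysis is biased or invalid, or that the trial is underpowered by its own standard. The document supports neither.

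Second, the gain is unknown. No correlation is given, and a low one is possible: the first CFS precedes the practitioner's explanation, and the second follows removal of the equipment. The document does not say that baseline fear is the strongest predictor; the factor it singles out for stratification is age. This stands, and it limits what can be said about size. It is not a reason against adjusting, since at low r almost nothing is lost.

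Third, the power figures use normal theory, whereas the plan may take the Mann-Whitney branch. The gain over that branch is not shown here. This stands.

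A reader might also infer that the post score and the change score are two competing answers. They are not: the post score is the sole primary outcome throughout, and the change score is plainly secondary and falls under the Holm adjustment. Nor is baseline CFS discarded, since it feeds that secondary outcome.

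**Conclusion.** The point holds as a recommendation on efficiency. The primary comparison omits a same-scale covariate collected before randomisation, together with the stratification factor, and the secondary change score does not make up for it. On the plan's difference and SD with 121 per arm, adjustment would raise power from 79% to about 83%, 89% or 97% at r = 0.3, 0.5 or 0.7, and to no more than 80.6% at r = 0.2 or less. These figures assume a two-sided test, equal SD before and after, approximate normality and a correlation that the document does not supply. The omission itself is certain from the text; its size is not. A result from the planned test would still be a valid randomised comparison.

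**What to change.** Before outcome data are analysed, pre-specify by amendment that the primary analysis is an ANCOVA of post-procedure CFS on arm, pre-procedure CFS and age stratum (5–11, 12–17), with robust standard errors, reported as an adjusted mean difference with its 95% confidence interval. For the primary outcome this replaces the choice between t-test and Mann-Whitney. Because the CFS is a discrete scale, an ordinal model with the same covariates could serve as a sensitivity analysis.

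The endpoint, the target difference and the sample size need not change. The change score can stay as a secondary outcome, since it is a stated objective and removing it is not needed for this purpose.

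The cost is small but goes beyond wording. Both covariates are already collected, so no new data are needed. However, the trial began on 21 January 2021 and is unblinded, so the change needs a dated amendment made without reference to outcomes by arm. If adjustment were decided after the results were seen, it would be open to the charge of being data-driven.

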### Trial design {8}

The study is designed as a randomised controlled monocenter superiority trial with two parallel groups, with the children’s anxiety as the primary outcome. The randomisation will be stratified for age with a 1:1 allocation.

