## Methods: participants, interventions and outcomes

### Study setting {9}

This study will be performed in the plaster room of the Amphia Hospital in Breda, The Netherlands.

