### Data collection and management

#### Plans for assessment and collection of outcomes {18a}

The following demographics of the patient are collected from the patient’s medical records: date of fracture, date of plaster intervention, age, sex, upper or lower extremity fracture, specific location of the fracture, type of plaster treatment (plaster replacement or removal) and previous experiences with plaster removal. After randomisation, additional demographic data is collected from the patient or accompanying parent/guardian and the orthopaedic practitioner before the plaster intervention (e.g. the use of pain killers, method of plaster removal (if applicable) and the video chosen (if assigned to the intervention group)).

Additionally, data is collected with short questionnaires before and after the procedure. The child’s anxiety and pain scores are collected before and after the procedure, using the Child Fear Scale [15] (CFS) and the Numeric Rating Scale (NRS pain), respectively. The child’s and parent’s satisfaction will be collected after the procedure using the NRS satisfaction.

Lastly, the child’s fastest heart rate (during the procedure) is collected with the finger pulse oximeter.

All data is collected by a single individual. The principal investigator will randomly check the data entry during the study.

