### Methods for additional analyses (e.g. subgroup analyses) {20b}

Descriptive statistics will be provided on the baseline demographic data.

Subgroup analyses will be performed, based on age (5–11 and 12–17), sex (female and male), type of plaster treatment (plaster removal and plaster replacement), method of plaster removal (saw and scissors compared to scissors only), the extremity fractured (upper and lower extremity), the specific location of the fracture (three most frequently found fractures in this study, presumably: distal radius, hand and distal humerus) [16], the use of painkillers and previous experiences with plaster removal.

The statistical package SPSS (version 25, IBM Corp, Armonk, NY, USA) will be used for all statistical analyses.

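### Previous experience with plaster removal, a planned subgroup factor, is sourced from medical records that may miss removals done elsewhere or years earlier; one question to the family would close the gap.

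*Protocol article*

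**What the plan says.** Outcomes {12} introduces one group of baseline items with "The following demographic data is collected from the patient’s medical records: date of fracture, date of plaster intervention, age, sex, upper or lower extremity fracture", and that list ends with "type of plaster treatment (plaster replacement or removal) and previous experiences with plaster removal". Plans for assessment and collection of outcomes {18a} repeats the list under the same source: "The following demographics of the patient are collected from the patient’s medical records". The two sections agree.

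Both sections then describe a second collection, made after randomisation: "additional demographic data is collected from the patient or accompanying parent/guardian and the orthopaedic practitioner before the plaster intervention". The examples given there are painkiller use, method of plaster removal and the video chosen. Previous experience is not among them, but the list is introduced as examples only.

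Methods for additional analyses {20b} closes its list of subgroup factors with "the use of painkillers and previous experiences with plaster removal". It names eight factors: age, sex, type of plaster treatment, method of removal, extremity, fracture location, painkiller use and previous experience.

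On the setting, Study setting {9} states: "This study will be performed in the plaster room of the Amphia Hospital in Breda, The Netherlands".

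The article does not say whether the record covers care at other hospitals or history reported by the family, how a record with no entry is coded, or whether the family confirms the entry.

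**The concern.** Previous experience is a fact about the child's whole life, whereas the named source is a record consulted in a single-hospital trial. Children are eligible up to age 17, so an earlier removal may lie years back or have taken place elsewhere. Background and rationale {6a} cites fracture prevalences of 40% in males and 28% in females aged 6 to 16, most of them treated with plaster. Earlier removals are therefore plausible, although those figures do not give the share of enrolled children who have had one.

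If a record without an entry is read as no experience, the error runs in one direction: experienced children move into the inexperienced subgroup, and none move the other way. That subgroup becomes a mixture, and any difference in the VR effect between first-time and experienced children shrinks towards zero. If the family is not asked at the visit, the analysis stage cannot readily recover the missing history. Yet the child and parent are already being questioned in the room.

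**Working it through.** **The plan's own figures.** The article gives no figure on this point. The sample-size inputs are used below, so they were checked first. Sample size {14} states "The expected anxiety score (CFS) in the control group is on average 1.78 ± 1.40", an improvement of 0.5, 80% power and alpha 0.05 (taken as two-sided). Then n per group = 2 × [1.40 × (1.96 + 0.84) / 0.5]² ≈ 123.07 with unrounded normal quantiles, against the stated 123; power at 123 per group is 0.800. The figure reproduces and does not depend on the subgroup factor.

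**Inputs for the misclassification (assumed; not in the documents).**
- p, the true share of children with a previous removal: 0.2 to 0.4.
- s, the share of those whose removal is in the record: 0.5 to 0.8.
- A silent record is treated as no experience.
- There are no false entries of experience.
- Children missed by the record respond to VR like the experienced children it captures.

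**Share misclassified.** Among children recorded as inexperienced, the share who are truly experienced is f = p(1 − s) / [p(1 − s) + (1 − p)].

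**Dilution.** The recorded-experienced subgroup is pure. The effect in the recorded-inexperienced subgroup is a weighted mean with weight f on the experienced effect. The observed difference between subgroups is therefore (1 − f) × the true difference.

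| p | s | f | A true difference of 0.50 appears as |
|---|---|---|---|
| 0.2 | 0.8 | 0.04 / 0.84 = 0.048 | 0.50 × 0.952 = 0.48 |
| 0.3 | 0.7 | 0.09 / 0.79 = 0.114 | 0.50 × 0.886 = 0.44 |
| 0.4 | 0.5 | 0.20 / 0.80 = 0.250 | 0.50 × 0.750 = 0.38 |

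A wider grid (p from 0.1 to 0.5, s from 0.5 to 0.9) gives f from 1% to 33%.

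**In children.** With 2 × 123 = 246 analysed, the middle case has 0.3 × 246 ≈ 74 truly experienced. The record shows 0.21 × 246 ≈ 52 of them, and about 22 sit in the wrong subgroup.

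**Power of the contrast.** Allocation is 1:1, so with share q in the experienced subgroup the standard error of the difference in effects is 1.40 × √[4/(246q) + 4/(246(1 − q))]. For a true difference of 0.50:
- Correct classification, q = 0.3: SE = 0.390, power = Φ(0.50/0.390 − 1.96) = 0.25.
- Middle case, q = 0.21 and apparent difference 0.443: SE = 0.438, power = Φ(0.443/0.438 − 1.96) = 0.17.

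Over the wider grid, power is 0.13 to 0.29 with correct classification and 0.08 to 0.24 with under-recording.

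**The case against.** The strongest objection is that the weakness of the record is inferred. A single-centre trial does not mean that the file holds only that centre's history: a record can contain outside care or history given by the family. This is right, and it rules out several stronger readings that a reader might infer:

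- **Only the family can report removals elsewhere, or misclassification is likely.** The article says nothing about how complete the records are or how many children were treated elsewhere. It supports no more than that experience may be under-recorded.
- **A silent record is coded as no experience.** No coding rule is given, and a category for unknown is not excluded. The direction of the error depends on this condition.
- **The true history is collected nowhere.** The items taken from the family are introduced as examples, so asking is not ruled out. Still, both sections assign this item expressly to the other source.

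The record also has merits. Its content does not depend on allocation, whereas the family items are collected after randomisation in a trial where no one is blinded. It is a sound source for removals at this hospital, including earlier ones for the present fracture. This argues against replacing it, but not against adding to it.

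Finally, the consequence is small. The contrast is poorly powered even with perfect classification, the middle-case loss is 0.06 points, and the worked difference of 0.50 is as large as the whole effect the trial is sized for. The article's stated directional subgroup hypothesis concerns age, not experience. All of this stands and sets the weight of the point. It does not remove a gap that can be closed at almost no cost.

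**Conclusion.** The point holds as a minor design improvement. The article fixes, in two places, a source that may miss removals done elsewhere or long ago, and uses the item to define a subgroup. There is no internal contradiction.

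If silent records are counted as no experience, about 5–25% of the recorded-inexperienced subgroup would be misclassified, and the difference between subgroups would shrink by the same proportion. That range rests wholly on the assumed 20–40% prevalence and 50–80% capture; the true size is unknown. The error should be non-differential by arm and is confined to one of eight low-powered subgroup factors. A reader should not infer any threat to the trial's main conclusion.

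**What to change.** Keep the record entry. Add one yes/no question, for the child and accompanying parent, to the questionnaire already completed before randomisation: has the child ever had a plaster removed, at this hospital or elsewhere, including earlier for this fracture? In Outcomes {12} and Plans for assessment {18a}, name both sources. In Methods for additional analyses {20b}, classify a child as experienced if either source says so.

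The question belongs before randomisation, not with the family items collected afterwards, so that the answer cannot be influenced by known allocation. Trial status gives a start date of 21 January 2021. For children enrolled before the change, the record would remain the only source, and this should be reported as a limitation.

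The cost is one extra question and slight recall error for distant events. Sample size and the primary analysis do not change.
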